# Concurrent exergaming and transcranial direct current stimulation to improve balance in people with Parkinson’s disease: study protocol for a randomised controlled trial

**DOI:** 10.1186/s13063-018-2773-6

**Published:** 2018-07-16

**Keywords:** Balance, Exergaming, Cognition, TMS, fNIRS

## Abstract

**Background:**

People with Parkinson’s disease (PD) commonly experience postural instability, resulting in poor balance and an increased risk of falls. Exercise-based video gaming (exergaming) is a form of physical training that is delivered through virtual reality technology to facilitate motor learning and is efficacious in improving balance in aged populations. In addition, studies have shown that anodal transcranial direct current stimulation (a-tDCS), when applied to the primary motor cortex, can augment motor learning when combined with physical training. However, no studies have investigated the combined effects of exergaming and tDCS on balance in people with PD.

**Methods/design:**

Twenty-four people with mild to moderate PD (Hoehn and Yahr scale score 2–4) will be randomly allocated to receive one of three interventions: (1) exergaming + a-tDCS, (2) exergaming + sham a-tDCS or (3) usual care. Participants in each exergaming group will perform two training sessions per week for 12 weeks. Each exergaming session will consist of a series of static and dynamic balance exercises using a rehabilitation-specific software programme (Jintronix) and 20 minutes of either sham or real a-tDCS (2 mA) delivered concurrently. Participants allocated to usual care will be asked to maintain their normal daily physical activities. All outcome measures will be assessed at baseline and at 6 weeks (mid-intervention), 12 weeks (post-intervention) and 24 weeks (3-month follow-up) after baseline. The primary outcome measure will be the Limits of Stability Test. Secondary outcomes will include measures of static balance, leg strength, functional capacity, cognitive task-related cortical activation, corticospinal excitability and inhibition, and cognitive inhibition.

**Discussion:**

This will be the first trial to target balance in people with PD with combined exergaming and a-tDCS. We hypothesise that improvements in balance, functional and neurophysiological outcome measures, and neurocognitive outcome measures will be greater and longer-lasting following concurrent exergaming and a-tDCS than in those receiving sham tDCS or usual care.

**Trial registration:**

Australian New Zealand Clinical Trials Registry, ACTRN12616000594426). Registered on 9 May 2016.

**Electronic supplementary material:**

The online version of this article (10.1186/s13063-018-2773-6) contains supplementary material, which is available to authorized users.

## Background

Parkinson’s disease (PD) is a chronic neurodegenerative disorder that affects approximately 1% of adults aged 60 years and older worldwide [1–3]. A prominent motor symptom of PD is postural instability, which typically worsens as the disease progresses, leading to impaired balance and increased risk of falls [4, 5]. The percentage of people with PD who experience a fall ranges from 46% to 55% [6–8], with falls contributing to injury, loss of independence and reduced quality of life (QoL) [5, 8–11]. Exercise is an effective treatment for improving balance in people with PD [4–7], and ongoing exercise training can be achieved through home-based training [8].

Exercise-based video gaming (exergaming) and immersive virtual reality modes have been used as part of home-based rehabilitation programmes to improve balance [9], and they may be as effective as conventional balance training in people with PD [10]. Exergaming combines physical movement with motion capture technology (e.g., Kinect®, Microsoft, Redmond, WA, USA; Wii®, Nintendo, Kyoto, Japan) to generate an on-screen avatar, which mimics the participant’s movements in real time. This is known as gesture-based interaction training [11], which combines automated game instructions as well as auditory and haptic inputs to correct performance and sustain motivation levels during and following game play [12–14]. For example, exergames for rehabilitation can provide auditory instructions to improve patient performance, such as ‘stand tall’ or ‘place your feet wider’, allowing patients to recognise deficits in movement and self-correct in real time [10, 15]. In addition, given that people with PD are dependent on sensory cues to overcome postural instability [16, 17], exergames employ visual and auditory feedback (termed *biofeedback*) techniques to create a quasi-immersive environment which can facilitate motor and cognitive learning [12, 18–22].

People with PD have difficulties with the long-term consolidation of new motor skills [23], but adjunctive neuromodulatory techniques, such as non-invasive brain stimulation, may help to upregulate neuroplasticity and facilitate motor skill acquisition and retention [24]. Transcranial direct current stimulation (tDCS) is a therapeutic tool that has been used to attenuate motor symptoms of PD [24, 25] with few side effects (e.g., occasional headache/nausea and scalp itchiness) [24]. When applied to the primary motor cortex (M1), anodal tDCS (a-tDCS) can induce a lasting increase in M1 excitability and reduce cortical inhibition, resulting in improved functional performance [26]. When combined with other training modalities such as exercise or physical therapy, greater and longer-lasting improvements in motor function have been observed in healthy and clinical populations than with either treatment modality alone [27–29]. However, no studies have investigated the concurrent use of a-tDCS and exergaming in people with PD.

The aims of this study are to determine the effects of a 12-week concurrent exergaming and a-tDCS intervention on measures of static and dynamic balance and to evaluate any long-term residual effects. Additionally, we will employ transcranial magnetic stimulation (TMS) techniques in the M1 and functional near-infrared spectroscopy (fNIRS) in the left and right dorsolateral pre-frontal cortices (DLPFC) to determine neurophysiological mechanisms that may underpin changes in balance. We hypothesise that the combination of exergaming and a-tDCS will lead to greater and longer-lasting improvements in balance and neurophysiological measures than exergaming or usual care alone.

## Methods/design

We will conduct a 24-week, exploratory, double-blind, randomised controlled trial to investigate the effects of a concurrent exergaming and a-tDCS intervention that includes a 12-week post-intervention follow-up period. Participants will be randomly allocated to one of three groups: (1) exergaming + a-tDCS, (2) exergaming + sham a-tDCS or (3) usual care (control). The trial will be conducted at the Institute for Physical Activity and Nutrition at Deakin University, Burwood, Melbourne, Australia. Ethical approval was granted by the Deakin University Human Research Ethics Committee (project number 2016-053), and the trial is registered with the Australian New Zealand Clinical Trials Registry (ACTRN12616000594426).

### Participants

A total of 24 men and women aged 55 years and older who have been diagnosed with mild to moderate PD (Hoehn and Yahr scale scores 2–4) will be invited to participate in this study.

### Recruitment

A list of people with PD will be compiled from an existing research study database at Deakin University and invited by telephone to participate in this trial. PD support groups within inner and outer suburban Melbourne will also be approached via mail or telephone to attend a study information seminar, which will be delivered by a member of the research team. All interested support group members will receive additional information pamphlets. Study advertisements will also be placed in the Australian Parkinson’s Disease Registry, in local newspapers and on noticeboards at community libraries. All participants who express an interest in the study will first be screened over the telephone, and eligible participants will then be required to come to Deakin University for additional screening as outlined below.

### Screening and eligibility

#### Telephone screening

All potential participants will be screened first over the telephone and will be eligible for this trial if they meet the following criteria: (1) have been diagnosed with PD by a neurologist, (2) have experienced one or more falls in the last 12 months, and (3) are not performing any regular physical therapy or structured exercise training. Participants will be ineligible based on the following criteria: (1) severe lower limb motor impairments and/or requirement of a walking aid or wheelchair, (2) previously diagnosed with stroke or dementia, (3) having metal implants in the head (i.e., deep brain stimulator or aneurysm clips), or (4) any other known medical, mental health or physical condition which may interfere with balance. Last, all participants need to be on a stable medication regimen for more than 6 weeks before proceeding to the on-site screening session.

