### Adverse events

The attending researcher will discuss what an adverse event (AE) is with each participant before the intervention begins. For this trial, an AE will be defined as any unfavourable and unintended sign, symptom or disease temporarily associated with the intervention (either exergaming or a-tDCS), without any understanding about causality or relationship to the therapy. The attending researcher will ask each participant before training begins about any AEs experienced and will document all AEs associated with the intervention. Usual care participants will be phoned and asked fortnightly about any experienced AEs. All AEs will be reported following the guidelines recommended by the National Health and Medical Research Council position statement (https://www.nhmrc.gov.au/guidelines-publications/e112). All participants will be asked to contact the attending researcher immediately after experiencing an AE, which will be recorded and promptly reported to the chief investigator, who will then determine its seriousness and causality in conjunction with any medical staff attending the event. Any AEs that are related to any part of the intervention will be reported to the Deakin University Human Research Ethics Committee.

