## Discussion

Falls among people with PD incurs a considerable cost associated with hospitalisation and injury management or treatment. An economic report published in 2014 established that health system costs due to accidental falls represent an additional 22% of the total health cost of PD [67]. This translates to an additional estimated annual cost of $1487AUD per person with PD [67]. Exergaming is a mode of exercise that is engaging, adds diversity to a rehabilitation programme, can be performed at home and may be effective at improving functional capacity and reducing risk of falls in people with PD. However, by combining exergaming with a-tDCS (a primer for adaptive neuroplasticity), greater and longer-term improvements in motor function may be achieved. To date, there is limited evidence for the effectiveness of combined exergaming and a-tDCS to improve balance and lower limb function in people with PD. As such, we aim to use a double-blind, randomised controlled study protocol to explore the efficacy of concurrent a-tDCS and exergaming for improving static and dynamic balance over a period of 12 weeks. In addition, our secondary objectives of using TMS and fNIRS to measure neurophysiological changes in the M1 and DLPFC will potentially provide a mechanistic understanding of any functional changes observed. Last, few studies have addressed the consolidation of long-term motor skill retention following exercise and a-tDCS in people with PD, and therefore we aim to explore any residual improvements in balance, lower limb and/or neurophysiological function after a 12-week follow-up period.

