In our study, exergames are used to deliver cognitive and static and dynamic balance exercises for people with PD. The Jintronix software used in our study is capable of using an inexpensive, commercially available motion capture camera to deliver a vast selection of rehabilitation games from a personal computer or laptop. Additionally, the use of a-tDCS to augment adaptive neuroplasticity may lead to greater and longer-lasting improvements in balance and lower limb function in people with PD. Thus, we hypothesise that (1) balance will improve for the exergaming groups compared with controls and (2) the addition of real a-tDCS will provide additive improvements. Novel home care therapies that are easily administered are likely to maintain exercise enjoyment and facilitate long-term exercise adherence. Therefore, if this trial is successful, this intervention will potentially allow for a high degree of scalability into a community- or home-based setting, where exergames can be implemented either as part of a rehabilitation programme in health-care facilities (i.e., rehabilitation hospitals, age care facilities and nursing homes) or as an adjunctive therapy that can be performed at home in conjunction with standard therapy. Our study also has the potential to have wider implications for reducing total health-care costs (i.e., hospitalisation, injury management and assistive care costs) associated with falls for people with PD.

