### Trial status

Eighteen participants have completed 24 weeks of training and are waiting to be tested at 3-month follow-up. No dropouts or adverse events have been reported.

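### All participants are recent fallers, but falls are not explicitly or comparably captured, so a report of no adverse events cannot be read as no falls

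*Protocol article*

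**What the plan says.** **Entry.** Under Telephone screening in the Protocol article, a person is eligible only if they "have experienced one or more falls in the last 12 months".

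**Motivation.** The Background puts the share of people with Parkinson's disease who fall at 46% to 55%, with no time window. The Discussion opens with the cost of falls, says exergaming "may be effective at improving functional capacity and reducing risk of falls in people with PD", and later adds: "Our study also has the potential to have wider implications for reducing total health-care costs", with falls named as the source of those costs.

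**Aim and outcomes.** The stated aim concerns effects "on measures of static and dynamic balance and to evaluate any long-term residual effects". The primary outcome is the Limits of Stability Test. None of the secondary or additional measures counts falls. The nearest is the Mini Balance Evaluation Systems Test, whose cut-off of 20 out of 28 classifies fall risk.

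**Safety.** The Adverse events section says "an AE will be defined as any unfavourable and unintended sign, symptom or disease temporarily associated with the intervention". It names exergaming and a-tDCS as the intervention and asks for no judgement of causality. Participants in training are asked about AEs before training, usual-care participants are phoned every fortnight, and everyone is asked to report an AE at once.

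**Status.** For 18 participants who have finished training, the article says: "No dropouts or adverse events have been reported".

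**The concern.** A fall is the event that every participant is known to be prone to, and the one the article uses to explain why the trial matters. With no fall count among the outcomes, the AE record is the only place a fall could appear, and its definition is a poor fit for that job.

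Two things are at stake. The first is the safety statement: a reader may take an absence of AEs in a group of fallers as reassurance about falls, which the recording rule cannot give. The second is comparability: if falls enter the record by different routes in different arms, even a descriptive comparison of arms could reflect how people were asked and not how often they fell.

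**Working it through.** The article states no figure on falls during the trial, so there is none to reproduce. The main check is of wording; the arithmetic only gives scale.

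**1. Which falls does the AE rule reach?**
- *Fall with injury, training arms.* The injury is a sign or symptom, and no causal link is needed. It would probably be recorded.
- *Fall without injury, training arms.* A fall is an event. Whether it is a sign, symptom or disease is left to the person recording it, as is whether a fall at home between sessions is associated with the intervention. Not clearly captured.
- *Any fall, usual care.* This arm receives neither exergaming nor a-tDCS, so read literally nothing that happens in it can be associated with them. Yet the arm is phoned about AEs. The definition and the questioning do not fit together.

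**2. Is the questioning alike across arms?** Training is twice a week for 12 weeks (2 × 12 = 24 sessions). If the pre-training question is asked at each session, that is up to 24 occasions. Fortnightly calls give 12/2 = 6 over the same period. After week 12 the training arms have no sessions, and no scheduled AE question is stated for them; no end date is given for the calls.

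**3. Scale, entry minimum.** Assume one fall per person-year continues, at a constant rate shared by all (Poisson, P(0) = exp(−expected)).
- 24 participants, 24 weeks: 24 × 24/52 = 11.1 expected falls.
- 18 participants, 12 weeks: 18 × 12/52 = 4.15; P(0) = exp(−4.15) = 0.016.
- Half the rate: P(0) = exp(−2.08) = 0.125.
- 18 participants, 24 weeks: 18 × 24/52 = 8.31; P(0) = exp(−8.31) = 0.0002.

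Twelve weeks is the safer exposure to use. Trial status speaks of 24 weeks of training, but the programme lasts 12 and follow-up testing is still awaited.

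**4. Scale, Background percentages.** Assume 46% to 55% is a 12-month risk p with constant hazard, so the chance that none of 18 falls in w weeks is (1 − p)^(18w/52).
- 12 weeks: 0.54^4.15 = 0.077; 0.45^4.15 = 0.036.
- 24 weeks: 0.54^8.31 = 0.006; 0.45^8.31 = 0.001.

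**5. Could falls have served as an efficacy outcome?** Under the same assumption the 24-week risk is 1 − 0.54^(24/52) = 0.25 to 1 − 0.45^(24/52) = 0.31. For a halving, p₂ = p₁/2, with n per arm, two-sided 5% level and p̄ the mean of p₁ and p₂:

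power = Φ{[(p₁ − p₂)√n − 1.96√(2p̄(1 − p̄))] / √(p₁(1 − p₁) + p₂(1 − p₂))}

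| Control risk | Power, 8 per arm | n per arm for 80% |
|---|---|---|
| 0.25 | 9% | 152 |
| 0.31 | 11% | 116 |
| 0.46 | 15% | 66 |
| 0.55 | 19% | 50 |

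**The case against.** The strongest reply has four parts.

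**The AE text does not exclude falls.** It asks for no causal judgement, leaves causality to the chief investigator afterwards, and has AEs asked about in all arms. A reader might infer that falls lie outside the definition and would go unseen. The documents do not support that: the text is silent on falls, and an injurious fall has a clear route into the record. This stands, and it limits the point to falls not being explicitly or comparably captured.

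**Falls need not be an outcome.** The trial calls itself exploratory, its aim is balance, and with 8 per arm power to detect a halving of fallers is below 20%. This stands in full. Selecting recent fallers does not oblige the trial to test falls, and the Discussion's remarks on falls and costs are hedged.

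**A condensed article may omit fall logs.** The full protocol and the content of the schedule figure are not at hand, and either could provide for falls. That is a fair limit on what can be said about missing outcomes. It does not answer the AE definition, which the article prints and which fits the usual-care arm badly as worded.

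**The expected-fall figures rest on an assumed rate.** One past fall is an entry condition, not a continuing rate. People selected for a recent event tend to regress towards the average, and variation between people makes zero more likely. This stands; the figures are illustrations.

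**Conclusion.** The point holds as a weakness in safety recording and in how the safety statement can be read. No listed outcome counts falls, the AE definition does not clearly include a fall without injury, and it cannot be applied literally to usual care. The status statement therefore says nothing dependable about falls.

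For scale, the chance of no falls among 18 participants over 12 weeks runs from 1.6% to 12.5% with the entry minimum and half of it, and from 4% to 8% with the Background percentages read as a 12-month risk. All of these assume a constant rate. A reader might infer that falls did occur and were missed. The figures do not show that, because the article reports no falls data in either direction; they show only that zero falls should not be presumed.

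**What to change.** 1. In the Adverse events section, state that any fall is recorded as an event in every arm, with or without injury and whether or not it is associated with the intervention.
2. Ask one identical fall question over the same recall window in all three arms to week 24, covering date, injury, and whether it happened during a session. The week 6, 12 and 24 visits suit this because every arm attends them. The fortnightly calls do not, since only usual care has them.
3. Report falls, fallers and injurious falls by arm as descriptive safety data, with no formal test.
4. For participants already past those visits, ask at the week 24 visit and label those falls as recalled.
5. Qualify the Trial status sentence to say that falls were not systematically recorded up to that point, if that is so.

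The cost is one question and one log line at visits already planned. The downsides are recall error for participants already through training, and counts too small to support more than description.

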#### On-site screening

The on-site screening session will be held at Deakin University, Burwood campus. During this session, participants will be required to complete the Montreal Cognitive Assessment, which is a 30-point screening instrument that assesses mild cognitive impairment (MCI). A cut-off score < 26 of 30 indicates the presence of MCI and will exclude participants from this trial [16, 30]. Participants will also be assessed using the motor section of the Unified Parkinson’s Disease Rating Scale (UPDRS), and individuals will be deemed eligible for the study only if they have mild to moderate PD (Hoehn and Yahr scale scores 2–4). All eligible participants will then be given a plain-language statement and consent form to sign and return prior to commencing the programme.

### Randomisation

Randomisation will be performed by a researcher independent from the study using computer-generated random numbers (Excel software; Microsoft). A flow diagram of the study protocol is provided in Fig. 1.

**Fig. 1 Fig1:**
[figure not shown]
Consolidated Standards of Reporting Trials (CONSORT) flow diagram of eligibility screening to the final follow-up assessment. *tDCS* Transcranial direct current stimulation

### Familiarisation

Following enrolment in the study and randomisation, participants will be asked to attend a familiarisation session at Deakin University. During this session participants allocated to the intervention groups will briefly practise all testing and intervention procedures. Participants allocated to the control group will only briefly undertake the testing procedures. As part of the intervention familiarisation procedure, all participants will perform a single set of each exergame while the objectives of each exergame are explained to them.

### Allocation and blinding

Following their enrolment in the study and after baseline testing, participants will be randomly allocated to one of three groups: (1) exergaming + a-tDCS, (2) exergaming + sham tDCS group or (3) a usual care control group. All groups will be stratified by sex to ensure equal distribution of male and female participants between groups. A researcher independent from the research team will pre-allocate a code for either real or sham a-tDCS, and the code will be given to the attending researcher to be input into the tDCS device during each training session. The identity of each code will be known only by the independent researcher to ensure double-blinding of both the attending researcher conducting the training session and the participant.

